# Protocol for a multicentre, parallel-arm, 12-month, randomised, controlled trial of arthroscopic surgery versus conservative care for femoroacetabular impingement syndrome (FASHIoN)

**DOI:** 10.1136/bmjopen-2016-012453

**Published:** 2016-08-31

**Keywords:** femoroacetabular impingement, hip impingement, hip arthroscopy, physiotherapy

## Abstract

**Introduction:**

Femoroacetabular impingement (FAI) syndrome is a recognised cause of young adult hip pain. There has been a large increase in the number of patients undergoing arthroscopic surgery for FAI; however, a recent Cochrane review highlighted that there are no randomised controlled trials (RCTs) evaluating treatment effectiveness. We aim to compare the clinical and cost-effectiveness of arthroscopic surgery versus best conservative care for patients with FAI syndrome.

**Methods:**

We will conduct a multicentre, pragmatic, assessor-blinded, two parallel arm, RCT comparing arthroscopic surgery to physiotherapy-led best conservative care. 24 hospitals treating NHS patients will recruit 344 patients over a 26-month recruitment period. Symptomatic adults with radiographic signs of FAI morphology who are considered suitable for arthroscopic surgery by their surgeon will be eligible. Patients will be excluded if they have radiographic evidence of osteoarthritis, previous significant hip pathology or previous shape changing surgery. Participants will be allocated in a ratio of 1:1 to receive arthroscopic surgery or conservative care. Recruitment will be monitored and supported by qualitative intervention to optimise informed consent and recruitment. The primary outcome will be pain and function assessed by the international hip outcome tool 33 (iHOT-33) measured 1-year following randomisation. Secondary outcomes include general health (short form 12), quality of life (EQ5D-5L) and patient satisfaction. The primary analysis will compare change in pain and function (iHOT-33) at 12 months between the treatment groups, on an intention-to-treat basis, presented as the mean difference between the trial groups with 95% CIs. The study is funded by the Health Technology Assessment Programme (13/103/02).

**Ethics and dissemination:**

Ethical approval is granted by the Edgbaston Research Ethics committee (14/WM/0124). The results will be disseminated through open access peer-reviewed publications, including *Health Technology Assessment*, and presented at relevant conferences.

**Trial registration number:**

ISRCTN64081839; Pre-results.

Strengths and limitations of this studyThis trial is multicentre, pragmatic and randomised, making results generalisable across the NHS.Further strengths include a large sample size and the robust procedures to assess treatment fidelity.The trial has a large sample size (344).There are robust procedures to assess treatment fidelity.

## Background

Until recently, there was little understanding of the causes of hip pain in young adults. Since first described in 2003, there has been increasing recognition of the syndrome of femoroacetabular impingement (FAI), which seems to account for a proportion of the previously undiagnosed cases of hip pain in young adults.^1^
^2^ Subtle deformities of hip shape combine to cause premature contact between the femoral neck and the acetabular rim which may result in hip pain.^1^
^3^ These shape abnormalities typically divide into three categories:^3^
^4^
Cam-type, in which the femoral head is oval rather than round, or there is bony prominence on the femoral neck;Pincer-type, in which the rim of the acetabulum is excessively prominent, in one or more areas of its circumference;Mixed-type hip impingement, a combination of cam and pincer types.

Surgery can be performed to reshape the bony contour of the proximal femur and/or acetabular rim in order to prevent impingement. Surgery for FAI has evolved more quickly than our understanding of the epidemiology or natural history of the condition,^5^
^6^ and is becoming an established treatment for FAI.^7^ The risks of complications from open surgery are greater than those for arthroscopic surgery and current evidence suggests that the outcomes of arthroscopic treatment for the symptoms of FAI are comparable to open surgery.^8^
^9^ Consequently, hip arthroscopy for FAI is a rapidly growing new cost pressure for health providers.^10^ However, a recently published Cochrane review highlighted the absence of randomised controlled trials (RCTs) comparing FAI surgery with conservative care such as physiotherapist-led exercise.^11^

Physiotherapy has also been shown to be beneficial in patients with FAI syndrome.^12^
^13^ During a successful feasibility study (HTA 10/41/02), a programme of physiotherapist-led conservative care was developed called personalised hip therapy (PHT).^14^

### Aims of trial

We aim to compare the clinical and cost-effectiveness of arthroscopic surgery versus physiotherapist-led conservative care (PHT) in patients with symptoms of FAI syndrome.

## Methods/design

This trial will be conducted in accordance with the Medical Research Council's Good Clinical Practice principles and guidelines, the Declaration of Helsinki, Warwick Clinical Trials Unit (WCTU) standard operating procedures (SOPs), relevant UK legislation and the trial protocol. Ethical approval was granted on 1 May 2014 (14/WM/0124), by the Edgbaston Research Ethics committee (current approved protocol V.3.1 20/01/2016). The trial will be reported in line with the CONSORT statement. This full trial follows a successful feasibility and pilot trial (HTA10/41/02).^14^

### Trial design and setting

This is a protocol for the **f**ull UK RCT of **a**rthroscopic **s**urgery for **h**ip **i**mpingement versus best c**on**servative care (**FASHIoN**). We will conduct a multicentre, pragmatic, assessor-blinded, parallel arm, 12 months, 1:1 RCT of hip arthroscopy versus conservative care for FAI assessing patient pain, function, general health, quality of life, satisfaction and cost-effectiveness. There is an integrated qualitative recruitment intervention that includes interviews with recruiters and patients, and observations of recruitment appointments to ensure patients have the opportunity to fully consider participation in the trial.^15^

We hypothesise that arthroscopic surgery is superior to conservative care at 12 months for self-reported hip pain and function for patients with FAI syndrome. The trial will be conducted on consenting patients treated in the NHS. Hospitals participating in FASHIoN will have an organised hip arthroscopy service treating at least 20 patients with arthroscopic surgery for FAI per year.

### Target population

We intend to recruit a cohort of typical patients with FAI deemed suitable for arthroscopic surgery. This included patients who may have already received a course of physiotherapy.

#### Inclusion criteria

Age ≥16 (no upper age limit);Symptoms of hip pain—patients may also have symptoms of clicking, catching or giving way;Radiographic evidence of pincer- and/or cam-type FAI morphology on plain radiographs and cross-sectional imaging, defined as:
Cam morphology—an α angle >55°;^16^Pincer morphology—a lateral centre edge angle of >40° or a crossover sign on the anteroposterior radiograph of the pelvis;^17^The treating surgeon believes the patient would benefit from arthroscopic FAI surgery;The patient is able to give written informed consent and to participate fully in the interventions and follow-up procedures.

#### Exclusion criteria

Evidence of pre-existing osteoarthritis, defined as Tonnis grade >1,^18^ or more than 2 mm loss of superior joint space width on anterio-posterior pelvic radiograph;^19^Previous significant hip pathology such as Perthes' disease, slipped upper femoral epiphysis or avascular necrosis;Previous hip injury such as acetabular fracture, hip dislocation or femoral neck fracture;Previous shape changing surgery (open or arthroscopic) in the hip being considered for treatment.

### Participant identification, invitation, recruitment and baseline data collection

Patients who complain of hip pain, who do not already have a diagnosis of hip osteoarthritis, will be identified as potential participants by screening referral letters to collaborating surgeons. Research nurses/associates will keep accurate screening logs to identify if these potential participants meet the eligibility criteria. Once diagnosed with FAI syndrome by the surgeon, and deemed eligible for the trial, the patient will be given a trial information sheet (see online supplementary files 1 and 2) and referred to a trained recruiter for a trial information consultation. During this consultation, patients can discuss the trial, participation will be offered and informed consent obtained (see online supplementary files 3 and 4). It will be explained that participation is voluntary and patients can withdraw at any time. Once consent is obtained, and prior to treatment allocation, baseline patient reported outcomes will be collected (see the Outcome measures section).

10.1136/bmjopen-2016-012453.supp1Supplementary data

10.1136/bmjopen-2016-012453.supp2Supplementary data

10.1136/bmjopen-2016-012453.supp3Supplementary data

10.1136/bmjopen-2016-012453.supp4Supplementary data

In order to optimise recruitment and informed consent, trained qualitative researchers will observe recordings of the surgeons' and research associate/nurses' trial information consultations (see online supplementary files 2 and 4), to identify communication patterns that facilitate or hinder patient recruitment^15^ (see figure 1). In-depth interview with the recruiters will be undertaken to identify clear obstacles and hidden challenges to recruitment, including the influence of patient preferences and equipoise.^20^ Research teams will be interviewed to identify clinician equipoise, patient pathway from eligibility to consent and staff training needs at each participating site.^15^ Findings will be fed back to the CI and trial management group, so that practice can be reviewed and any necessary changes (including additional training) implemented. The number of eligible patients, the percentages of these that are approached and consented to be randomised will be monitored at each site.

**Figure 1 BMJOPEN2016012453F1:**
[figure not shown]
Participant flow diagram.

This research will be linked, through [name], to the Quintet programme of research within the MRC ConDuCT-II (Bristol) Trial Methodology Hub.

### Randomisation

Participants will be randomised, in a 1:1 ratio, to arthroscopic surgery or PHT using a computer-generated sequence. Allocation will be made by the research nurse/associate via a centralised telephone randomisation service provided remotely by WCTU. Allocation concealment will be ensured, as the randomisation programme will not release the randomisation code until the patient has been recruited into the trial. In order to improve baseline balance between intervention group samples, a minimisation (adaptive stratified sampling) algorithm will be implemented using study site and impingement type (cam, pincer or mixed) factors. Research nurses/associates who recruit participants will ensure they are referred for the allocated intervention. Patients and clinicians cannot be blind to treatment allocation. However, outcome assessors will be blind to the treatment delivered.

### Interventions

The two interventions will start as soon as possible after randomisation. We will record dates of randomisation and the start of allocated treatment. As this is a pragmatic trial, participants were not prohibited from undergoing any additional/concomitant care.

#### Arthroscopic surgery

Arthroscopic surgery will be completed by a Consultant Surgeon delivering hip arthroscopy as part of their routine practice. Arthroscopic hip surgery will be performed under general anaesthesia according to the surgeon's usual practice. Shape abnormalities and consequent labral and cartilage pathology will be treated. Bony resection at the acetabular rim and at the head–neck junction will be assessed by intraoperative image intensifier radiographs and/or satisfactory impingement-free range of movement of the hip. Patients will be allowed home when they can walk safely with crutches (usually within 24 hours). On discharge, patients will be referred for a course of rehabilitation as per usual care for that surgeon. We will not specify a protocol for this postoperative physiotherapy, but will record the surgeons' routine postop care and any case-by-case changes to this. Care will be taken to ensure that physiotherapists delivering postoperative care to FASHIoN trial participants are different from those trained and providing PHT in order to avoid contamination between groups. Patients will also have a postoperative MRI after 6 weeks.

In order to ensure the fidelity of the surgery and to identify participants for a secondary analysis, a panel of international experts will review operation notes, intraoperative images and postoperative MRI scans to assess whether adequate surgery was undertaken. This panel includes: [name] (USA), [name] (Switzerland), [name] (Australia) and [name] (UK).

#### Personalised hip therapy

PHT is a package of physiotherapist-led best conservative care for FAI. It was developed during the feasibility study and ‘road-tested’ during the pilot trial (HTA 10/41/02).^14^ The care being offered represents a consensus of what physiotherapists, physicians and surgeons regard as ‘best conservative care’ for FAI. PHT will be delivered by a senior physiotherapist at each site, who will be trained at a FASHIoN PHT workshop, and supported in PHT delivery by a physiotherapy research facilitator.

PHT consists of four key components:
An assessment of pain, function and range of hip motion,Patient education and advice,Help with pain relief (which may include up to one radiographic-guided intra-articular steroid injection where pain prevents performance of the exercise programme),An exercise programme that has the key features of individualisation, progression and supervision.

The intervention is delivered over a minimum of six patient contacts (at least three of which must be face-to-face treatment contacts, others can be by telephone and email) over a period of 6 months. In situations where the patient needs additional review, support or guidance, further sessions with the physiotherapist are permitted up to a maximum of 10 contacts. Evidence of exercise individualisation, supervision and progression will be sought from individual participant physiotherapy case report forms (CRFs). Accuracy of CRFs will be audited against the physiotherapist's treatment notes.

The PHT CRFs will be assessed for intervention fidelity to identify participants for a secondary analysis by the panel that developed the protocol for PHT, including: [name] (Senior Academic Research Physiotherapist), [name] and [name] (UK; Extended Scope Musculoskeletal Physiotherapists) and PW (Academic Orthopaedic Surgeon).

Crossover of participants between interventions can be problematic in trials of this nature. In order to minimise, this care will be taken prior to enrolment in the trial to ensure potential participants:
Are willing to receive either intervention,Understand both treatments are thought to provide benefit,Are willing to remain with their allocation for 12 months,Understand that both interventions may take 6 months to improve symptoms.^12^
^19^

In instances where patients are not satisfied with how their treatment is progressing prior to reaching the primary outcome, they will be able to have a further consultation with their treating surgeon where they would be treated in their best interests.

### Risks and benefits

Both interventions are thought to provide benefit in patients with FAI. The short-term risks of this study relate to the two interventions. These risks are described below and inform the expected serious adverse events (SAEs).

Hip arthroscopy requires a general anaesthetic. The risk of complications from hip arthroscopy is about 1–2%. These include:
Infection—thought to be <1 in 1000.Bleeding—possibly causing bruising or a local haematoma.Traction-related—in order to perform hip arthroscopy, traction is required to separate the hip joint surfaces. Sometimes after the procedure, the pressure from the traction can cause some numbness in the leg. The numbness usually resolves within a few hours or days.Osteonecrosis—during surgery, the blood supply to the hip joint could be damaged. However, there are no reported cases of osteonecrosis following arthroscopic FAI surgery.Femoral neck fractures—this is also a very rare complication. This complication would require a further procedure to fix the fracture.

#### Personalised hip therapy

There are some small risks with pain medications and joint injection. However, the main risk is muscle soreness and transient increases in pain from the exercises that will be undertaken.

### Outcome measures

Baseline data will be collected from participants once consent is obtained and prior to randomisation. Follow-up questionnaires will be administered centrally by a data clerk via post. If participants fail to respond, they will be contacted via telephone, email or via their next of kin where necessary. Table 1 lists the data collected and at which follow-up time points.

**Table 1 BMJOPEN2016012453TB1:** Data collection time points

Time point	Data collection
Baseline	Demographics, physical activity (UCLA Activity Scale),^29^ iHOT-33, SF-12,EQ-5D Preoperative imaging, economics questionnaire
Intervention	Operation notes and photographs; or PHT log. Complications records 6 weeks post start of intervention. Postoperative MRI (surgery intervention only)
6 months	iHOT-33, SF-12, EQ-5D, resource usage, adverse events
12 months (primary outcome)	iHOT-33, SF-12, EQ-5D, patient satisfaction, resource usage, adverse events
2 years	Further procedures questionnaire
3 years	Further procedures questionnaire
5 and 10 years	Linkage to National Joint Registry and HES to identify need for hip replacement

### Primary outcome

The primary outcome measure is hip pain, function and hip-related quality of life using the **International Hip Outcome Tool-33** (iHOT-33) at 12 months following randomisation. iHOT-33 is a validated hip-specific patient-reported outcome tool which measures health-related quality of life in young, active patients with hip disorders.^21^ It consists of the following domains: symptoms and functional limitations, sports and recreational activities, job-related concerns and social, emotional and lifestyle concerns.

We chose it following our feasibility and pilot study as:
It is more sensitive to change than other hip outcome tools,^21^It does not show evidence of floor or ceiling effects in patients undergoing hip arthroscopy,^21^Patients were involved extensively in item generation; so we can be confident that it measures what is most important to patients,^21^There is an independently determined minimally clinically important difference (MCID),^21^It is used as the principal outcome measure for the UK Non-Arthritic Hip Registry; mandated for arthroscopic FAI surgery by the National Institute of Health and Care Excellence (NICE).^10^

### Secondary outcome measures

#### Health-related quality of life: EQ-5D 5L

This is a validated measure of health-related quality of life, consisting of a five-dimensional health status classification system and a separate visual analogue scale. EQ-5D is applicable to a wide range of health conditions and treatments and provides a simple descriptive profile and a single index value for health status.^22^ Responses will be converted into health utility scores using established algorithms.^23^

#### *General health*: Short Form-12 Health Survey V.2

This is a validated and widely used health-related quality-of-life measure, particularly including hip conditions and treatments.^24^ SF-12 is able to produce the physical and mental component scales originally developed from the SF-36 with considerable accuracy but with far less respondent burden.^25^ Responses will be converted into health utility scores using established algorithms.^26^

#### Patient satisfaction

Using questions that our team ([name]) has used in previous trials with musculoskeletal pain patients,^27^ we will measure two distinct dimensions of satisfaction in all participants during follow-up: ‘*Overall, how satisfied are you with the treatment you received?’* and ‘*Overall*, *how satisfied are you with the results of your treatment?’* Responses are on a 5-point Likert scale. These questions are in line with previous studies of patient satisfaction which show that the majority of patients express overall satisfaction with the care they received, but fewer express overall satisfaction with the clinical outcomes resulting from their care.

#### Qualitative assessment of outcome

We will conduct in-depth interviews one-to-one with a purposively selected sample of 25–30 participants in each of the trial groups, including older and younger, male and female, more and less active and more and less satisfied participants recruited at different trial sites. The qualitative interviews will supplement the quantitative outcomes. Interviews will explore experiences of the trial processes, the treatments and the consequences of treatment to participants' lives, health and well-being.

#### Adverse events

We will record the number and type of adverse events (AEs) up to 12 months. Any AEs will be reported on the appropriate CRF and returned to WCTU. Any SAEs will be faxed to WCTU, within 24 hours of the local investigator becoming aware, where the Chief Investigator will determine causality and expectedness. SAEs deemed unexpected and related to the trial will be reported to the research ethics committee within 15 days.

#### Resource usage

Information on healthcare resource use will be collected by incorporating questions within the patient follow-up questionnaires. We confirmed the feasibility and acceptability of this approach in our pilot trial, and patient self-reported information on service use has been shown to be accurate in terms of the intensity of use of different services.^28^

#### Need for further procedures

We will record any further treatments performed in both groups, such as hip arthroscopy, open hip preservation surgery, hip replacement or additional ‘out of trial’ physiotherapy. We propose to ascertain the need for further procedures by questionnaire at 2 and 3 years. We also propose a 5 and 10-year no-cost ascertainment of hip replacement by linkage to the UK National Joint Registry (NJR) and Hospital Episode Statistic (HES) databases.

### Sample size calculation

The development work for iHOT-33 reported a mean iHOT-33 score of 66 and an SD of 19.3 in a heterogeneous population with a variety of hip pathologies. The baseline iHOT-33 data from our pilot trial (HTA grant 10/41/02) suggests the target population of patients being considered for hip arthroscopy for FAI have lower scores with less variability, with a mean of 33 and SD of 16. The MCID for iHOT-33 in this population is 6.1 points.^21^

Our sample size calculation is therefore based on an SD of 16 and a between-group MCID of 6.1: a standardised effect difference between groups at 12 months of 0.38. The expected sample size for 90% power to detect an effect size of 0.38 at 12 months, at a 5% significance level, assuming an approximately normal distribution of the iHOT-33 score is 292. Allowing for 15% loss to follow-up at 12 months, we will recruit a sample of 344 participants over 26months in the UK (172 in each group).

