### Statistical analysis

The primary analysis will be of differences in hip-related quality of life (iHOT-33) at 12 months between the two treatment groups, blinded, on an intention-to-treat basis and presented as the mean difference between the trial groups with a 95% CI. iHOT-33 data will be assumed to be normally distributed; possibly after appropriate variance-stabilising transformation.

The minimisation randomisation procedure should ensure treatment group balance across recruiting sites. We have no reason to expect that clustering effects will be important for this study, but the possibility of such effects will be explored as part of the analysis.^33^ We plan to account for clustering by generalising a conventional linear (fixed-effects) regression approach to a mixed-effects modelling approach; where patients are naturally grouped by recruiting sites (random-effects) and, if amenable to analysis, also by physiotherapist and surgeon. This model will formally incorporate terms that allow for possible heterogeneity in responses for patients due to the recruiting centre, in addition to the fixed effects of the treatment groups, and patient characteristics that may prove to be important moderators of treatment effect such as age, gender and FAI type. This analysis will be conducted using specialist mixed-effects modelling functions available in the software packages Stata (StataCorp. 2015. Stata Statistical Software: Release 14. College Station, Texas, USA: StataCorp LP) and R (http://www.r-project.org/). All tests will be two-sided and considered to provide evidence for a statistically significant difference if p values are <0.05 (5% significance level).

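### The 90% power for the 12-month comparison rests on a baseline SD of 16, with no 12-month SD and no reason given why the baseline spread should hold after treatment

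*Protocol article*

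**What the plan says.** All of the following is in the protocol article.

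- **Two SDs** (Sample size calculation). One is from the instrument's development work: "The development work for iHOT-33 reported a mean iHOT-33 score of 66 and an SD of 19.3 in a heterogeneous population". The other is from the pilot trial's baseline data, where patients considered for arthroscopy "have lower scores with less variability, with a mean of 33 and SD of 16".
- **The choice** (same section). "Our sample size calculation is therefore based on an SD of 16 and a between-group MCID of 6.1", expressed as "a standardised effect difference between groups at 12 months of 0.38".
- **The result** (same section). "The expected sample size for 90% power to detect an effect size of 0.38 at 12 months" is given as 292, with alpha set to 5% and scores taken as roughly normal. A 15% allowance for loss to follow-up raises this to 344, or 172 per group.
- **The analysis** (Statistical analysis). "The primary analysis will be of differences in hip-related quality of life (iHOT-33) at 12 months between the two treatment groups". Tests are two-sided at 5%. Age, gender and FAI type are named as examples of patient characteristics in the model; baseline iHOT-33 is not named. The Methods paragraph of the abstract describes the primary comparison as one of change in iHOT-33.
- **Data collected** (Outcome measures, Table 1). iHOT-33 is recorded at baseline, 6 months and 12 months.

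**The concern.** Power for a comparison of 12-month scores depends on the between-patient SD of those scores, or on the residual SD if the model adjusts for covariates. The SD used was measured before treatment, in patients selected for surgery whose mean score was 33.

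The stated reason for preferring 16 to 19.3 is that 16 comes from the target population. That settles who is measured but not when. Both treatments are expected to help, so scores should move, and nothing in the article says whether the spread moves with them.

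The standardised effect of 0.38, the 292, the 344 and the 90% all depend on this one SD. If the 12-month SD is larger and no precision is gained from adjustment, a true 6.1-point difference will be missed more often than the stated 10%. A non-significant result would then carry less weight than a reader relying on 90% power would give it.

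**Working it through.** **Inputs from the article:** difference 6.1; SD 16 (pilot baseline); SD 19.3 (instrument development); two-sided alpha 0.05; power 90%; 1:1 allocation; 15% loss. SDs of 22 and 25 and all correlations below are assumptions.

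**1. Reproduce the plan.**

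Standardised effect: 6.1/16 = 0.381, stated as 0.38.

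Per group: n = 2(1.960 + 1.282)²/0.38² = 145.5, so 146 per group and 292 in all. A t-test calculation with the unrounded 6.1/16 also gives 292.

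Recruitment: 292/0.85 = 343.5, so 344. Both stated figures are right.

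**2. Vary the 12-month SD, unadjusted, 146 per arm.**

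The standard error of the difference is SD × √(2/146). Power is from the noncentral t. The last column is the difference detectable with 90% power, which scales with the SD from 6.09 at SD 16.

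| 12-month SD | Standard error | Power for 6.1 | Detectable at 90% |
|---|---|---|---|
| 16 | 1.87 | 90.1% | 6.09 |
| 18 | 2.11 | 82% | 6.85 |
| 19.3 | 2.26 | 76.8% | 7.35 |
| 22 (assumed) | 2.57 | 66% | 8.37 |
| 25 (assumed) | 2.93 | 55% | 9.52 |

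The normal approximation differs by at most 0.3 percentage points (77.0% at 19.3). At SD 19.3, 90% power for 6.1 points would need 424 evaluable by the t calculation, or 422 by the normal approximation. If all 344 were followed up, power at 19.3 would be 83%.

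**3. Adjust for baseline iHOT-33.**

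Effective SD = 19.3 × √(1 − r²), where r is the baseline to 12-month correlation.

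| r (assumed) | Effective SD | Power |
|---|---|---|
| 0.3 | 18.4 | 81% |
| 0.5 | 16.7 | 87% |
| 0.6 | 15.4 | 92% |

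The effective SD returns to 16 when r = √(1 − (16/19.3)²) = 0.56.

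**4. Analyse change from baseline, SD 16 at both times.**

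SD of change = 16 × √(2(1 − r)).

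| r (assumed) | SD of change | Power |
|---|---|---|
| 0.3 | 18.9 | 78% |
| 0.5 | 16.0 | 90% |
| 0.6 | 14.3 | 95% |

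Unequal SDs can also give about 16. With 16 at baseline, 19.3 at 12 months and r = 0.6, the SD of change is √(16² + 19.3² − 2 × 0.6 × 16 × 19.3) = 16.06, and power is again about 90%.

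**The case against.** The strongest defence is that the sponsor made a reasoned choice. It had two SDs and took the one from its own target population. The other is from mixed hip pathologies, which can itself widen an SD, and the article does not say when it was measured. Replacing 16 by 19.3 exchanges one SD not shown to be a 12-month SD for another, from a less relevant population. This stands, so 77% is only one point in a sensitivity range. A reader might infer that the trial's true power is 77%; the article does not support that.

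A reader might also infer that the spread must widen after treatment as responders and non-responders separate. That is plausible, but the article offers no evidence for it. Equally, it offers none that the spread stays at 16.

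Third, baseline iHOT-33 is collected, and the final covariates may be left to an analysis plan that is not shown. Adjustment could restore 90% or more. This stands too, and the absence of baseline iHOT-33 from the named covariates is not in itself a fault. But the sample size section takes no credit for adjustment, so a later gain would not supply the missing basis for the 90%.

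Fourth, on the abstract's description of a change analysis, one might say that 16 is right only with equal SDs and a correlation of 0.5. Step 4 shows otherwise: other combinations give the same SD of change, and power can fall on either side of 90%.

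Fifth, results will be reported as a mean difference with a 95% CI, whose width reflects the observed SD. This limits the harm from an optimistic planning SD. Pilot data will also be pooled with the main trial data; if pilot participants are additional to the 344, which the article does not say, the evaluable number would exceed 292.

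**Conclusion.** The point holds as an unsupported planning assumption, not as an arithmetic error. A reader might take it to mean that 292 or 344 was miscalculated; both are correct for the inputs used.

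What the article does not support is an unconditional 90%. Without adjustment, that figure requires a 12-month SD of about 16, and the only evidence for 16 is from before treatment. At the article's other SD the chance of missing a true 6.1-point difference would be 23% (100 − 77) rather than 10%, and the difference detectable with 90% power would be about 7.35 points. Adjustment for baseline could remove that loss if the correlation is about 0.56 or higher. The article gives neither the correlation nor the 12-month SD, so the size of any shortfall is unknown, and there may be none.

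**What to change.** 1. Keep the recruitment target at 344.
2. Say in the sample size section that the 90% is conditional on the pilot baseline SD of 16 holding at 12 months. The section already identifies the source of the 16; it needs to state the condition.
3. Report power and the detectable difference over a range of 12-month SDs, for example 16 to 25, unadjusted and adjusted for baseline across a stated range of correlations, with the assumed values marked as such.
4. Include baseline iHOT-33 as a covariate in the primary model, and make the abstract and the Statistical analysis section agree on whether the comparison is of 12-month scores or of change.

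A check of the SD on 12-month data is optional. It would have to be done with the arms combined, so that nothing about the treatment difference is revealed. It would also have to be reconciled with the Data management section, which rules out analysing outcomes until all primary outcome data are in, and with the plan to pool pilot data into the final analysis.

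The cost is a reworded paragraph and one covariate already collected. No extra patients are needed. The stated power becomes a range, part of which is below 90%.
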